### Evaluation of adverse events

Safety parameters are evaluated for each rTMS stimulation. Information relating to the adverse event, date of onset, date of resolution, severity, treatment, outcome, seriousness, and relationship to rTMS will be described in the medical record and case report form. When the relationship to rTMS cannot be ruled out, follow-up observations will be performed as much as possible until recovery to normal conditions. The terms used to describe adverse events conform to those provided by the Medical Dictionary for Regulatory Activities/Japanese version (MedDRA/J): International Conference on Harmonization (ICH).

The safety evaluation parameters are as follows:

Adverse events, particularly headache, stimulation site pain, stimulation site discomfort, presence or absence of muscle contraction (evaluated each time rTMS is delivered).The presence or absence of suicidal ideation (a parameter related to suicide in HAMD-17) and YMRS score (evaluated each time during the acute treatment and observation periods).

The results of the safety evaluation parameters should be recorded on the case report each time they are evaluated.

The severity of each adverse event is defined as follows:

Mild: the condition in which the participant feels discomfort but does not interfere with daily life.Moderate: the condition that restricts the participant’s daily life and makes the participant feel uncomfortable.Severe: the condition wherein the participant is unable to work or perform daily activities.

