### Definition of terms

The terms of the endpoints of this study are defined as follows:

Response: A response will be defined as a decrease of ≥50% in the HAMD-17 score measured at week 0 during the acute treatment period or a total HAMD-17 score of ≤12.Remission: The presence of remission will be defined as a total HAMD-17 score of ≤7.Relapse/recurrence: When a participant experiences conditions that meet the diagnostic criteria for depressive, manic, or hypomanic episodes defined in the DSM-5 after remission, during the acute treatment period, such conditions will be defined as relapse/recurrence. Additionally, relapse will be defined as disease exacerbation within half a year of remission, and recurrence will be defined as disease exacerbation after more than half a year of remission.

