#### Secondary endpoints

The secondary endpoints will be as follows:

Response/remission maintenance rate during the observation period.Relapse/recurrence rate during the observation period.The time to relapse or recurrence during the observation period from the time origin is defined as end of the acute treatment.The change in scores of the MADRS, HAMD-17, Patient Health Questionnaire-9 (PHQ-9) (18), Clinical Global Impression (CGI) (19), Young Mania Rating Scale (YMRS) (20), EuroQol 5 Dimensions (EQ-5D) (21), Brief Assessment of Cognition in Schizophrenia Japanese version (BACS-J) (22), and THINC-integrated tool (THINC-it) (23) during the acute treatment and observation periods.Adverse events, particularly headache, pain at the stimulation site, discomfort at the stimulation site, and muscle contraction on stimulation.Suicidal ideation (suicide subscale score of HAMD-17) and manic switch (YMRS score).

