### Criteria for discontinuation of individual study participant

If the principal investigator, principal investigator, or sub-principal investigator determines that it is not feasible to continue research on an individual research subject for any of the following reasons, the research on that research subject will be terminated. With full consideration given to the ethical aspects of study subjects, information on observations and tests related to the primary and secondary endpoints will be collected after the point of discontinuation to the greatest extent possible.

Withdrawal of consent or request for withdrawal to participate by the study participants.It is revealed after enrollment that the eligibility criteria were not met.Suicidal ideation is exacerbated (HAMD-17 score for suicide, ≥3) and continuation of the study is considered unfavorable.The total YMRS score is ≥8.The occurrence of an adverse event makes it difficult to continue the study.Pregnancy.Significantly poor compliance (rTMS is performed 2 days or less in 2 consecutive weeks).Occurrence of a convulsive seizure.Relapse/recurrence during the observation period.Discontinuation of the entire study, andThe investigator considers it appropriate to discontinue the study for other reasons.

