### Definition of case classification

Eligible cases: the participants who meet all the inclusion criteria and do not meet any of the exclusion criteria.

Discontinued cases: the participants who discontinued the study according to the criteria of discontinuation of individual case.

Handling the data of discontinued cases or missing values:

Discontinued casesFor the FAS, the values measured until the discontinuation time will be used for evaluation irrespective of the discontinuation time. For the PPS, the discontinued cases will be treated as missing values if the participant discontinues the study <4 weeks from the start of the study. Measured values will be used if the participant discontinues the study >4 weeks after the start of the study.Missing valuesThe primary endpoint, the MADRS total score, will be analyzed using mixed-effects models for repeated measures (MMRM) including those patients who had some missing values. Moreover, sensitivity analyses will be performed using single imputation methods such as baseline observation carried forward (BOCF) that performs an evaluation by substituting values measured at baseline for missing values and last observation carried forward (LOCF) by substituting the last measured value prior to the missing values. As for multiple imputation, distributions are assumed for the missing values with different parameters of the distribution according to conditions such as treatment methods. Additionally, a supplementary complete case analysis will be performed with participants having no missing data during the period of acute phase treatment.The time (days) to relapse or recurrence during the observation period, a secondary endpoint, will be defined as the interval (days) from the first day of the observation period to the date when the relapse or recurrence was identified. If a patient had not come to hospital before week 28 of the observation period, two types of handling of data will be considered; one is that the relapse or recurrence date will be regarded as 7 days after the final evaluation date, and the other is that the observation will be treated as censored on the final evaluation date. If no relapse or recurrence is confirmed at 28 weeks, the observation will be treated as censored on the day of 28 weeks.

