#### Other endpoints

The response and remission rates at week 4 in the acute treatment period and at week 28 in the subsequent observation period will be analyzed using logistic regression analysis, in which the MADRS total score at week 0, intervention, diagnosis, age, and institution will be explanatory variables. As a secondary analysis, Fisher test will be used. For MADRS, HAMD-17, PHQ-9, CGI, YMRS, EQ-5D, BACS, and THINC-it, a comparison between the active and sham stimulation groups will be performed using Wilcoxon rank-sum test at week 4 during the acute treatment period and at week 28 in the subsequent observation period, respectively.

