### Adverse events

The number of cases and proportion of adverse events in the active and sham stimulation groups will be calculated during the acute treatment period and in the subsequent observation period, respectively. Both groups will be compared and analyzed using chi-square test or Fisher test.

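### Patients stopped early for a raised YMRS drop out of the only stated YMRS comparison, which is therefore selected on the outcome; an any-time count should be added

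*Protocol article*

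**What the plan says.** All places are in the protocol article.

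- **Secondary endpoints** lists score changes on eight scales, YMRS among them. A separate item reads "Suicidal ideation (suicide subscale score of HAMD-17) and manic switch (YMRS score").
- **Criteria for discontinuation of individual study participant** lists "The total YMRS score is ≥8" among the reasons to stop. Every reason on that list applies only if an investigator determines that continuing is not feasible. The suicide-item reason (3 or more) carries a further condition of its own; the YMRS reason does not.
- The same section says that "information on observations and tests related to the primary and secondary endpoints will be collected after the point of discontinuation to the greatest extent possible".
- **Definition of case classification** restricts the FAS, for discontinued patients, to what was measured up to the point of stopping. For the per protocol set, "the discontinued cases will be treated as missing values if the participant discontinues the study <4 weeks from the start of the study".
- **Other endpoints** says that, for a list of scales including YMRS, "a comparison between the active and sham stimulation groups will be performed using Wilcoxon rank-sum test at week 4 during the acute treatment period", and likewise at week 28. No other test of YMRS is stated. The HAMD-17 suicide item has no stated comparison of its own.
- **Evaluation of adverse events** has the suicide item and "YMRS score (evaluated each time during the acute treatment and observation periods") recorded as safety parameters.
- **Adverse events** counts cases by arm and period: "Both groups will be compared and analyzed using chi-square test or Fisher test".
- **Definition of terms** counts as relapse or recurrence conditions that "meet the diagnostic criteria for depressive, manic, or hypomanic episodes defined in the DSM-5 after remission". The time-to-relapse analysis covers patients in remission at week 4.

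**The concern.** A patient whose YMRS rises to 8 in week 2 and who is then stopped has the event that the endpoint is meant to capture. Under the FAS wording that patient has no usable YMRS at week 4 or week 28. The patients compared at those visits are mostly those who did not have the event. If active stimulation caused more switches, more patients would leave the active arm's comparison, and the remaining scores could look alike. The scores that triggered the stops are recorded session by session, but no stated analysis of this endpoint uses them.

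The article's Introduction names manic switch as a risk in this population, and safety is part of the trial's stated objective. At stake is whether the YMRS comparison can reflect an excess of switches at all.

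**Working it through.** **1. Arm size.** The plan's own figure is 38 analysed per arm, from an effect size of 0.65, two-sided alpha of 0.05 and power of 0.80. Check: n = 2 × (1.960 + 0.842)² / 0.65² = 15.70 / 0.4225 = 37.2, rounded up to 38. Dividing, 38 / 0.80 = 47.5, rounded up to 48 consented. Both figures reproduce, and 38 per arm is used below.

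**2. The rules applied to one patient.** YMRS first reaches 8 in week 2 and the investigator stops the patient.
- FAS: values count up to week 2, so there is none at week 4 or week 28.
- Per protocol set: stopped before 4 weeks, so treated as missing.
- Missing-data methods: the mixed model, LOCF, BOCF and multiple imputation are set out around the MADRS primary endpoint. None is named for YMRS.
- Result: absent from both Wilcoxon comparisons. A patient who first reaches 8 at the week-4 or week-28 visit itself is still counted there.

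**3. What that does to a result.** Suppose 1 sham and 8 active patients are stopped in this way.
- The week-4 Wilcoxon test compares 38 − 1 = 37 with 38 − 8 = 30 patients, none of whom has switched before that visit.
- The any-time count is 1/38 = 2.6% against 8/38 = 21.1%, a difference of 7/38 = 18.4 points. Fisher p = 0.028.
- Wald standard error: √(0.0263 × 0.9737/38 + 0.2105 × 0.7895/38) = √0.00505 = 0.071. The 95% interval is 18.4 ± 1.96 × 7.1, or about 4.5 to 32.3 points (approximate at such counts).

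**4. Simulation.** The documents give no switch risks and no YMRS distribution, so every input here except the arm size and the threshold of 8 is an assumption.

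First set (4,000 trials per row): non-switchers' YMRS is Poisson(1.5) capped at 7 in both arms. Switchers score 8–19 and are stopped before week 4. Entries are the percentage of trials with p < 0.05.

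| Assumed risk, sham vs active | Wilcoxon, stopped dropped | Wilcoxon, baseline carried forward | Wilcoxon, triggering score carried forward | Fisher, any YMRS ≥8 |
|---|---|---|---|---|
| 3% vs 10% | 5.0 | 4.9 | 8.6 | 6.9 |
| 3% vs 20% | 5.0 | 5.4 | 24.9 | 51.4 |
| 5% vs 25% | 4.8 | 4.8 | 34.6 | 61.8 |
| 0% vs 15% | 5.0 | 5.0 | 21.2 | 52.7 |

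Second set (3,000 trials per row, Poisson(2) capped at 7, sham risk 2.5%): Wilcoxon with stopped patients dropped rejects 4.2–4.4% throughout. The Fisher test rejects 8%, 57% and 91% at active risks of 10%, 20% and 30%.

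The flat 5% follows by construction. Once switchers are removed and everyone else has the same distribution, the test has nothing left to detect. The simulation shows what the written rules imply under those inputs; it does not predict this trial's results.

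**The case against.** Five points deserve a fair hearing.

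- **The Wilcoxon test is not called the manic-switch test.** Its list of scales mirrors the score-change endpoint, which is separate from the manic-switch item. A reader might infer that the protocol has chosen this test for manic switch; the article does not say so, and a dedicated tabulation may sit in an analysis plan not shown. This stands. What remains is that the one YMRS comparison the article does fix is selected on the outcome.
- **Stopping is not automatic, and data may continue.** A reader might infer that the rule deletes every switcher. It does not: an investigator must decide, and endpoint data are then to be collected where possible. But the FAS wording leaves later values unused, so the two statements conflict. Even if later values were used, a week-4 score taken after a switch need not show that one occurred.
- **Mania is captured elsewhere.** A reader might infer that the trial would be blind to mania. That is too strong: a switch reported as an adverse event enters the chi-square or Fisher comparison, and a manic or hypomanic episode after remission counts as relapse. Neither route is tied to a YMRS value, however. Relapse requires prior remission, and the time-to-relapse analysis covers only week-4 remitters.
- **The power gain depends on large assumed risks.** This stands. At 3% versus 10% the Fisher test rejects 6.9% of the time, slightly below the 8.6% for Wilcoxon with the triggering score carried forward.
- **YMRS of 8 or more is nowhere defined as a switch, and entry sets no YMRS limit.** This also stands, and the fix allows for it.

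**Conclusion.** The concern holds in a limited form. Following the stated rules, patients stopped before week 4 or week 28 for a raised YMRS contribute nothing to the YMRS comparison at those visits, and no stated analysis counts them from the YMRS record. The provision for collecting data after discontinuation conflicts with the FAS wording, and the two passages must be reconciled.

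Under the assumed inputs, the fixed-week Wilcoxon test without stopped patients rejects about 5% of the time whatever the excess. The any-time Fisher test rejects about 51–57% at 20% versus 2.5–3%, and about 7–8% at 10% versus 2.5–3%. At a modest excess the gain is therefore a count and interval not selected on the outcome, rather than power. The size rests on switchers being stopped before week 4, no later values being used, and equal scores in all other patients.

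This is a worthwhile, inexpensive improvement to a secondary safety endpoint. Nothing here touches the primary MADRS analysis, and it is not a defect that must be cured before the trial can be interpreted.

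**What to change.** - Add a prespecified analysis of the proportion of FAS patients with a YMRS total at or above the protocol's own discontinuation threshold (8) at any post-baseline assessment, counting the value that triggered discontinuation. Report both proportions, the risk difference with its confidence interval, and a Fisher test.
- Report baseline YMRS by arm, and handle separately any patient already at 8 or above at baseline.
- Do the same for a HAMD-17 suicide item of 3 or more. That score is an exclusion criterion at entry, so baseline cases should be rare.
- Keep the week-4 and week-28 score comparisons as supportive.
- Reconcile the discontinuation section with the FAS definition by stating whether YMRS and suicide-item values obtained after discontinuation are used.

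The stopping rules stay as they are. The cost is analysis wording and two added analyses of limited power. The scores are already recorded at each session, and the article says that recruitment is still open and that unblinding waits for data fixation, so the change can still be prespecified.

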### Analytical method

#### Primary endpoints

The change in MADRS total scores from weeks 0 to 4 during the acute treatment period will be analyzed using MMRM, in which the MADRS total score at week 0 as well as the interaction between the total score at week 0 and time point as continuous covariates (fixed effects), and the intervention, age, diagnosis, institution, time point, and interaction between the intervention and time point as categorical variables (fixed effects), and the response variables included will be the change in MADRS total scores measured at weeks 2 and 4. An unstructured covariance model will be fitted to intra-individual covariance structure, and Kenward–Roger degrees-of-freedom (DF) method will be applied to estimate the DF. The hypothesis test will be performed based on the least square estimates. Main comparison between the interventions will be performed by contrast at 4 weeks. As sensitivity analyses, analysis of covariance (ANCOVA) after LOFC, after BOCF for missing data at 4 weeks, and complete case ANCOVA will be performed. As secondary analyses, the change in the MADRS total score from weeks 0 to 4 will be analyzed using Wilcoxon rank-sum test. Interim analysis will not be performed.

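### The secondary scales rest on a rank test that ignores baseline, and the text conflicts on whether week-28 scores after relapse are used

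*Protocol article*

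**What the plan says.** All references are to the protocol article.

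- **Other endpoints.** Eight scales are covered: three of depression (MADRS, HAMD-17, PHQ-9), together with CGI, YMRS, EQ-5D, BACS and THINC-it. The planned analysis is this: "a comparison between the active and sham stimulation groups will be performed using Wilcoxon rank-sum test at week 4 during the acute treatment period". The same test is then repeated, with the timing given as "at week 28 in the subsequent observation period, respectively". No covariates are named. The logistic regressions for response and remission in the same section do adjust, for week-0 MADRS, diagnosis, age and institution.
- **Outcomes, Secondary endpoints.** The endpoint for these scales is "The change in scores of the MADRS, HAMD-17, Patient Health Questionnaire-9" and the rest of the list, so a week-0 score is needed for each.
- **Analytical method, Primary endpoints.** MADRS to week 4 is analysed by an MMRM that includes "the MADRS total score at week 0 as well as the interaction between the total score at week 0 and time point as continuous covariates". The rank test is secondary there: "As secondary analyses, the change in the MADRS total score from weeks 0 to 4 will be analyzed using Wilcoxon rank-sum test".
- **Criteria for discontinuation of individual study participant.** The list of reasons includes "Relapse/recurrence during the observation period". It applies when an investigator "determines that it is not feasible to continue research on an individual research subject for any of the following reasons". The same section plans to go on collecting primary and secondary endpoint data after discontinuation, as far as can be managed.
- **Definition of case classification.** For discontinued patients, the full analysis set (FAS) uses the scores obtained up to discontinuation.
- **Definition of terms.** Relapse or recurrence can occur only after remission.

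**The concern.** There are two separate issues.

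First, the test for the scales does not adjust for baseline. If it is applied to changes, baseline is subtracted with a fixed coefficient of one, which adds noise unless baseline and follow-up are highly correlated. If it is applied to raw scores, baseline is not used at all. Either way the test is less precise than an adjusted model on the same data, and it gives no baseline-adjusted treatment effect. The plan does better for MADRS at week 4, and it adjusts the response and remission models, so the scales are treated differently without a stated reason.

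Second, two passages pull apart at week 28. One has data collected after a patient is discontinued for relapse. The other ends the patient's contribution to the FAS at discontinuation. Read literally, a score obtained after relapse would be collected and then left out. The week-28 scale comparisons and the response and remission regressions would then be conditioned on an event after randomisation that treatment may affect.

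**Working it through.** **The plan's own figure.** Inputs from Number of participants: effect size 0.65, two-sided alpha 0.05, power 0.80.

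n per group = 2 × (1.960 + 0.842)² / 0.65² = 37.2, rounded up to 38. Then 38 / (1 − 0.20) = 47.5, rounded up to 48. Both stated figures reproduce. A two-sample t-test with 38 per group has power 0.799.

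**Week-4 power: inputs.** n = 38 per arm and d = 0.65 on the week-4 SD (set to 1). The correlation ρ between week 0 and week 4 is not given; 0.3, 0.5 and 0.7 are assumed. Normal data are assumed, with equal SDs at both visits.

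**Formulas.**
- SD of change = √(2(1 − ρ))
- Residual SD after baseline adjustment = √(1 − ρ²)
- Rank test: effective n = 38 × 3/π = 36.3, from its asymptotic relative efficiency of 0.955
- Noncentrality = (0.65 / SD) × √(n/2). Power is from the noncentral t, with 73 degrees of freedom for ANCOVA and 2n − 2 (about 71) for the rank test

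| | ρ = 0.3 | ρ = 0.5 | ρ = 0.7 |
|---|---|---|---|
| SD of change | 1.183 | 1.000 | 0.775 |
| Residual SD, ANCOVA | 0.954 | 0.866 | 0.714 |
| Noncentrality, Wilcoxon on change | 2.34 | 2.77 | 3.58 |
| Noncentrality, ANCOVA | 2.97 | 3.27 | 3.97 |
| **Power, Wilcoxon on change** | **0.64** | **0.78** | **0.94** |
| Power, Wilcoxon on raw score | 0.78 | 0.78 | 0.78 |
| **Power, ANCOVA** | **0.83** | **0.90** | **0.98** |

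The gap between Wilcoxon on change and ANCOVA is about 20, 12 and 3 percentage points. A simulation of 4,000 trials per setting agrees: Wilcoxon on change 0.63, 0.78 and 0.94; ANCOVA 0.83, 0.89 and 0.97.

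**Where the loss comes from.** At ρ = 0.5 a t-test on change has power 0.80, so ranks cost about 2 points. The other 10 or so come from not adjusting for baseline.

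**Sensitivity to scaling.** If 0.65 is placed on the SD of change instead, the ANCOVA effect is 0.65 × √(2/(1 + ρ)) = 0.806, 0.751 and 0.705. Its power is 0.93, 0.90 and 0.86, against 0.78 for Wilcoxon on change. The adjusted analysis leads in every setting.

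**Week 28.** No arithmetic is possible. The shift in an arm's mean equals the share of patients whose scores are left out, times the difference in mean score between those left out and those kept. The article gives neither quantity for either arm. What can be shown is the conflict: relapse is a discontinuation reason, later data are to be collected, and the FAS stops at discontinuation.

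**The case against.** **On week 4.** A rank test is valid under randomisation and reasonable for a coarse scale such as the seven-stage CGI, or for YMRS, where a total of 8 or more is itself a discontinuation criterion. The primary comparison is already baseline-adjusted, and these analyses sit under other endpoints. All of this stands, and it limits the weight of the point. It does not remove it, because the article fixes the unadjusted test as the sole analysis and the better model is already in use for MADRS.

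**On week 28.** A reader might infer that the week-28 tests compare only patients who did not relapse. The article does not fix that. Discontinuation depends on an investigator's determination, collection continues afterwards, and patients who never remitted cannot relapse by definition and so stay in.

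A reader might also infer that a benefit through relapse prevention would be lost to the trial. It would not: relapse/recurrence rate, maintenance of response or remission, and time to relapse are separate secondary endpoints, and time to relapse has Kaplan–Meier, log-rank and Cox analyses.

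Finally, a missing-data rule for secondary endpoints is commonly left to the full protocol or SAP, so its absence from an article is no fault. What stands is narrower: the FAS rule that is stated would leave unused the data that the discontinuation section says will be collected.

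**Conclusion.** The point holds in two parts, and neither touches the primary MADRS comparison.

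1. The scales are analysed by an unadjusted rank test where a baseline-adjusted model would be more precise. At 38 per arm and d = 0.65 on the week-4 SD, adjustment is worth about 20, 12 and 3 points of power over Wilcoxon on change at ρ = 0.3, 0.5 and 0.7. Against Wilcoxon on raw scores it is worth about 5, 12 and 20 points. The correlations are assumptions, and so is applying to the other scales an effect size that was set for the sample size. The direction does not depend on either.
2. The discontinuation section and the FAS rule conflict on post-relapse data. Read literally, this restricts the week-28 comparisons by an event that treatment may affect. The documents give no basis for a number, and any stated bias in scale points would rest on invented relapse rates and scores.

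**What to change.** **Scales.** Make a baseline-adjusted ANCOVA or MMRM the main analysis of each scale. Include the scale's own week-0 score, the other covariates of the primary model (age, diagnosis, institution) and the stratification factors (sex and age group). Keep the Wilcoxon test as supportive, for example for CGI and YMRS, and say whether it is applied to changes or raw scores. The cost is modest programming and reliance on a model assumption; no new data are needed.

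**Week 28.** Reconcile the discontinuation criteria, the FAS rule and the Other endpoints section so that scores collected after discontinuation are used at week 28. Where a patient relapsed and no later score exists, count that patient as not in remission at week 28. Do not assign a worst rank on every scale: a depressive relapse is not the worst outcome on a mania scale, and no relapse is by itself the worst outcome on the cognitive tests. The cost is a change of wording. Recruitment is still open and unblinding comes only after the data are fixed, so both changes can be made before unblinding.
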